##### Sample size calculation

Sample size was calculated assuming the worst proportion for an item, based in the previous published literature, which was chest congestion, that occurred in a prevalence of 75,7%, then assuming a confidence interval of 0,95% and a  $\alpha=0,05$  (with a standard normal deviate for a two-sided  $\alpha$ ), the required number would be 280 participants. This sample is adequate for the target factorial analysis in which 24 items will be used (WURSS-21 + headache, body ache and fever). For controls comparison and predictive validity evaluation, assuming that WURSS has a Sensitivity of 0,85 and Specificity of 0,44, and the fact that 70% of the population experiences a cold in a given year[9, 39], for a desired precision of 0,05 for the sensitivity and for a specificity of 0,1 the sample size population needed will be 281 participants. The largest population of 281 patients will be chosen as target for evaluation.

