## 4.METHODS

### 4.1. Participants and Study Design

#### 4.1.1. Cross-cultural translation and validation of a respiratory infection symptom questionnaire (I)

This is a trans-sectional case control validation research project of a respiratory symptoms questionnaire to be applied in a three months follow-up period during the seasonal peak of upper respiratory infection from January to March 2012 in patients over 16 years old with and without respiratory infections.

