#### 4.3.1. Cross-cultural translation and Validation of WURSS (I)

For statistical analysis of questionnaire validation factorial analysis will be used for content validity evaluation using the 7 identified domains of WURSS-21 plus headache, body-ache and fever, which are included in WURSS-24. This approach combines exploratory and confirmatory procedures, using weighted least square estimates employing diagonal weight matrix techniques to seek common factors between the domains; all questioned items will be included in the analysis. Convergent validity will be provided by Pearson correlations between WURSS-21 scores in the first day and SF-36 scores in the third, as this measures health state in the last 4 weeks. For criterion validity sensitivity, specificity and predictive positive values will be calculated, as well as area under the curve. For internal consistency Cronbach's alpha coefficient in each domain based on the average of scores from the first three days will be calculated and also comparison between the first and last day. To evaluate each day, responsiveness index will be calculated which is equal to minimal important differences (MID)/ $\sqrt{(2\text{mean squared error})}$ .

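### Study I: the 281 participants meet the stated precision for sensitivity only; the same inputs give 316 for specificity, and the case share and predictive value need a separate correction

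*Protocol*

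**What the plan says.** Protocol section 4.1.1 describes Study I as a "trans-sectional case control validation research project". Cases are patients with physician-diagnosed respiratory infection, recent onset and a qualifying Jackson score. Controls are patients attending for non-respiratory reasons. No case:control ratio is given.

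The sample size text under section 4.3.1 makes two calculations. The first, on the proportion reporting a single item, gives 280. The second concerns the comparison with controls. It starts from "assuming that WURSS has a Sensitivity of 0,85 and Specificity of 0,44", adds "the fact that 70% of the population experiences a cold in a given year", and concludes: "for a desired precision of 0,05 for the sensitivity and for a specificity of 0,1 the sample size population needed will be 281 participants". The text then closes: "The largest population of 281 patients will be chosen as target for evaluation".

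On analysis, section 4.3.1 says: "For criterion validity sensitivity, specificity and predictive positive values will be calculated, as well as area under the curve".

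**The concern.** The second calculation has two precision targets, so the required number is the larger of two results. The stated 281 looks like the sensitivity result alone. If so, the claim that it also delivers the specificity precision is wrong as written.

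Two further matters sit beside this. The 70% is the chance of a cold over a year in the population, whereas in a case-control sample the investigators' recruitment sets the share of cases. And a predictive value depends on that share, so a value read directly from the sample could be taken for clinical performance when it partly reflects how many controls were enrolled.

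**Working it through.** **Inputs** (Protocol, sample size calculation under 4.3.1)
- Sensitivity 0.85 and specificity 0.44.
- Precision: "for a desired precision of 0,05 for the sensitivity and for a specificity of 0,1", read as half-widths of 95% confidence intervals.
- Case share 0.70, hence 0.30 controls.
- z = 1.96. The two-sided 5% level is stated for the first calculation ("with a standard normal deviate for a two-sided" alpha) and is assumed to carry over to the second.

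**Formula.** Number in the relevant group = z² × p × (1 − p) / d². Divide by that group's share to get the total.

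**Sensitivity (reproduces the plan's figure)**
- 1.96² × 0.85 × 0.15 / 0.05² = 195.9, so 196 cases.
- 195.9 / 0.70 = 279.9, so 280 in total. This matches the stated 281 to within one participant.

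**Specificity**
- 1.96² × 0.44 × 0.56 / 0.10² = 94.7, so 95 controls.
- 94.7 / 0.30 = 315.5, so 316 in total.

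The requirement from the protocol's own inputs is the larger figure, 316.

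**What 281 gives at 70:30**
- Cases: 281 × 0.70 = 196.7. Controls: 281 × 0.30 = 84.3.
- Sensitivity half-width: 1.96 × √(0.85 × 0.15 / 196.7) = 0.0499.
- Specificity half-width: 1.96 × √(0.44 × 0.56 / 84.3) = 0.106.

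**Can another split of 281 meet both?**
- Sensitivity needs a case share of at least 195.9 / 281 = 69.7%.
- Specificity needs a control share of at least 94.7 / 281 = 33.7%.
- These add to 103.4%, so no split works. The smallest total is 196 + 95 = 291, at about 67.4% cases. At 50% cases the total is 392 and sensitivity is the limiting target.

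**Alternative methods**
- Wilson interval: 196 cases and 91 controls. The specificity total at 30% controls is 91 / 0.30 = 303.3, so 304, and the free-split minimum is 196 + 91 = 287. Both exceed 281.
- z = 2: 291.4 for sensitivity and 328.5 for specificity.
- One-sided z: 197.1 and 222.2. Both fall below 281, but this does not reproduce 281 and contradicts the stated two-sided level.

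**Predictive value by case share s.** PPV = 0.85s / [0.85s + 0.56(1 − s)].

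| Case share | PPV |
|---|---|
| 70% | 0.595 / 0.763 = 78% |
| 50% | 0.425 / 0.705 = 60% |
| 20% | 0.170 / 0.618 = 27.5% |

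**The case against.** **The shortfall is not demonstrated.** The protocol fixes no ratio, so 95 or more controls may be enrolled among 281 and the specificity target would then be met. That is correct: a reader might infer that the study will miss its specificity precision, and the documents do not show this. What stands is that the sentence claiming both precisions at 281 is wrong. With 95 controls, 186 cases remain and the sensitivity half-width becomes 1.96 × √(0.85 × 0.15 / 186) = 0.051, so the other target is missed slightly.

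**281 may mean cases only.** The Summary speaks of participants with respiratory infections and of 281 patients. On that reading sensitivity would be estimated to 1.96 × √(0.85 × 0.15 / 281) = ±0.042. But section 4.3.1 derives 281 for the comparison with controls, and on the cases-only reading no number of controls is stated anywhere. The ambiguity is a further reason to give the two numbers separately.

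**The 70% is not the cause.** One might infer that the annual rate produced the miss. It did not: taken at face value it already gives 316. The larger requirement was simply not carried forward. Nor does a planning input affect an estimated predictive value; that problem comes from enrolling by status.

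**The predictive value is not worthless.** The protocol does not say that raw sample proportions will be used, and the value can be computed from sensitivity and specificity at a chosen prevalence. The objection therefore applies to the raw sample value only.

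**The 280 from the item calculation.** One might argue that all 280 must be cases, because the 75.7% is a proportion among people with a cold. The protocol states neither the denominator nor the precision. Assuming ±0.05 gives 283, close to 280, but this is an assumption, so the argument is not made here.

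**Conclusion.** The stated number is wrong as written, but the consequence is small. The protocol's inputs give 280 for sensitivity and 316 for specificity, and 281 covers only the first. At 70:30 the specificity half-width is ±0.106 instead of ±0.10, and meeting both targets takes at least 291 with a free choice of split. This rests on reading the precisions as half-widths at two-sided 5%, a reading that the reproduced sensitivity figure supports.

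Two separate points also hold. An annual population cold rate does not justify a case share in this design, and a raw positive predictive value from the sample would move with recruitment. Overall severity is minor: this is a precision statement for one accuracy measure in an observational validation study, and no hypothesis test depends on it.

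**What to change.** 1. Correct the sample size statement. Either keep 281 and give the specificity precision as about ±0.106 at 70:30, or state the requirement as 316 at 70:30, or as 196 cases plus 95 controls (291).
2. Give the planned cases and controls as two numbers, drop the annual cold rate as the source of the case share, and say whether 281 includes controls.
3. In the criterion validity analysis, replace the raw sample predictive value with likelihood ratios (at the assumed values, 0.85 / 0.56 = 1.52 for a positive result and 0.15 / 0.44 = 0.34 for a negative one), or with predictive values computed from sensitivity and specificity at stated external prevalences.

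Restating the precision and changing the reported measures costs only wording. Meeting both targets costs 10 more participants than planned with a free split, or 35 more at 70:30. Whether recruitment can still change is unclear: section 4.1.1 dates the study to January–March 2012, before the protocol's date of December 2012, while the milestones place validation at month 34 of a project that began in September 2010. If recruitment has closed, report the achieved numbers of cases and controls with the precision they give.

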#### Participants

All patients that require an unscheduled appointment due to acute illness in a primary health care center (USF Progresso, Perafita, Unidade Local de Saúde de Matosinhos) and from the Department of Allergy and Clinical Immunology from Centro Hospitalar de São João will be recruited. The inclusion criteria for respiratory infections cases are: over or equal 16 years of age, physician diagnosis of respiratory tract infections, with onset of symptoms within 48h and with Jackson score for respiratory infections over 3 or higher. In Jackson score eight symptoms (sneezing, nasal discharge, nasal obstruction, sore throat, cough, headache, malaise and chilliness) are classified as 0=absent, 1=mild, 2=moderate or 3=severe and presence of at least one of the first four cold specific symptoms is required for diagnosis. All those patients that attend to the primary care center or allergy department for other reason except respiratory symptoms/infections will be proposed to enroll the study project as controls. Exclusion criteria are: under 16 years of age, all patients with basal or throat symptoms that started more than 48h before they searched medical care. Results provided from patients with allergy and those without allergy complains will be compared for changes in respiratory symptoms score and in quality of life changes.

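### Study I takes the larger of 280 and 281, but 280 is most plausibly a count of ill respondents and 281 is derived as a total of ill and non-ill participants, so a mixed total of 281 does not deliver the 280

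*Protocol*

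**What the plan says.** Section 4.3.1 of the Protocol, under Sample size calculation, contains two derivations.

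- **Item frequency.** The least frequent item, chest congestion, is taken from earlier literature: "that occurred in a prevalence of 75,7" per cent. With a two-sided 5% normal deviate, "the required number would be 280 participants". No precision is printed. The text then adds: "This sample is adequate for the target factorial analysis in which 24 items will be used".
- **Diagnostic accuracy.** For the comparison with controls, the inputs are sensitivity 0.85 (precision 0.05), specificity 0.44 (precision 0.1) and "the fact that 70% of the population experiences a cold in a given year". The result is 281.

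The paragraph closes: "The largest population of 281 patients will be chosen as target for evaluation".

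Section 4.1.1 enrols people with and without respiratory infection. Attenders without respiratory complaints "will be proposed to enroll the study project as controls", and both groups complete the WURSS. No case-to-control ratio and no separate number of cases is given. The Summary and the Portuguese Resumo mention only participants with respiratory infections for this study and repeat the 281.

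**The concern.** Choosing the larger of two sample sizes satisfies both requirements only if both count the same kind of participant. Here one formula includes a division by the proportion with a cold and the other does not. If the divided figure is a total that includes controls, reaching 281 does not supply the number of ill respondents that the other calculation asked for.

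At stake is the stated basis for the Study I sample size. The precision behind the 280 would not be delivered, and the sentence that calls the sample adequate for the 24-item factor analysis would refer to a number of respondents that a case-only analysis may not have.

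**Working it through.** **Inputs from Section 4.3.1:** item frequency 0.757; sensitivity 0.85 with precision 0.05; specificity 0.44 with precision 0.10; share with a cold 0.70; two-sided alpha 0.05, so z = 1.96; 24 items. **Assumed:** item precision ±0.05, which is not printed.

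Formula throughout: n = z² p(1 − p) / d².

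1. **Reproducing 280.** 1.96² × 0.757 × 0.243 / 0.05² = 282.7, so 283 against the printed 280. Solved the other way, 280 implies d = 1.96 × √(0.757 × 0.243 / 280) = 0.0502. The assumed ±5 points is therefore the precision that 280 carries. There is no division by a case share.

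2. **Reproducing 281.** 1.96² × 0.85 × 0.15 / 0.05² = 195.9, so 196 to 197 ill patients. Undivided, this is far from 281. Divided by 0.70 it gives 196/0.70 = 280 and 197/0.70 = 281.4. The specificity inputs do not give 281: 1.96² × 0.44 × 0.56 / 0.10² = 94.7, and 94.7/0.30 = 315.5. So 281 is the sensitivity requirement scaled up to a total of ill plus non-ill participants.

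3. **Ill patients in a total of 281.** At the 70% used in its derivation: 281 × 0.70 = 196.7, about 197 ill, and 281 × 0.30 = 84.3, about 84 controls. This is 83 fewer ill patients than 280.

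4. **Item precision with 197 ill.** 1.96 × √(0.757 × 0.243 / 197) = 0.0599, or ±6.0 points.

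5. **Other case shares (assumed range).**

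| Case share | Ill patients in 281 |
|---|---|
| 50% | 141 |
| 70% | 197 |
| 90% | 253 |

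All are below 280.

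6. **Pooling cases and controls.** Assume almost no chest congestion in controls. The pooled frequency is 0.70 × 0.757 = 0.53, and the half-width at 281 is 1.96 × √(0.53 × 0.47 / 281) = 0.058, or ±5.8 points. With 0% to 20% chest congestion in controls, the pooled frequency is 0.53 to 0.59 and ±5 points would need about 383 to 372 participants.

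7. **Respondents per item.** 280/24 = 11.7; 197/24 = 8.2.

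8. **If 281 counts ill patients only.** The half-width is 1.96 × √(0.757 × 0.243 / 281) = 0.0501, so the item calculation is met. But step 2 shows that the formula asks for only 196 to 197 ill patients, so 281 is not its result in that unit, and no number of controls is given anywhere.

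**The case against.** Several points on the other side are sound.

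- **The 70% is not a planned case share.** It is an annual population risk of a cold used as a prevalence input. A reader might infer that the plan fixes 197 cases and 84 controls; it does not. Those numbers are conditional. What stands without them is that 281 was obtained by dividing by 0.70 and 280 was not.
- **The 281 may mean ill patients.** The Summary and Resumo can be read this way, and the closing sentence of Section 4.3.1 speaks of patients. A reader might infer that the first calculation is missed outright; on this reading it is met. The derivation of 281 and the enrolment of controls in Section 4.1.1 favour a mixed total but do not prove it.
- **The 280 is labelled participants, not ill patients.** That a lowest item frequency of 75.7% describes people with a cold is a plausible inference from a source not at hand. The pooled reading also misses ±5 points, although that rests on an assumed frequency in controls.
- **The factor analysis is not restricted to cases.** It is tempting to conclude that about 8 respondents per item is too few. The documents do not support that: they give no subjects-per-item criterion and do not say who enters the analysis.
- **The practical effect is small.** Estimating an item frequency is not among the analyses listed in Section 4.3.1; the formula serves only to choose n. Sensitivity is a listed analysis, and its precision is met with about 197 cases.

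These points limit the size and certainty of the shortfall. They do not put 280 and 281 on the same basis.

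**Conclusion.** The point holds in conditional form: the paragraph compares two numbers with different units, and the target cannot be relied on to meet both calculations.

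- **If 281 is the total:** ill patients number below 280 at every case share examined. At 70% there are about 197, and item precision is about ±6.0 points in place of ±5.0. Pooling gives about ±5.8.
- **If 281 is ill patients only:** the item calculation is met, but the figure is not what its formula yields and the controls have no target.

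The size rests on three assumptions: the back-solved ±5 points, the 75.7% describing ill respondents, and 70% serving as the case share. The difference in basis needs none of these. The error lies in how the sample size is justified; no listed analysis is shown to fail.

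**What to change.** Rewrite the sample size paragraph in Section 4.3.1:

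1. State for each of 280 and 281 whether it counts ill patients or all participants, and print the precision used for 280.
2. Delete the choice of the larger figure.
3. Then take one of two routes. Either keep 281 as the total, state the expected numbers of cases and controls, and give the resulting item precision (about ±6.0 points at a 70% case share). Or define 281 as cases, give the number of controls separately, and make the Summary and Section 4.1.1 agree.
4. State whether the factor analysis uses cases only. If it does, tie the adequacy statement to the cases actually expected (about 8 per item at 197 cases) and not to 280.

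The cost is the rewording of one paragraph, with a matching line in the Summary if needed. Under the first route no extra participants are required; the stated item precision becomes about one point wider. Under the second, a control number has to be set, and the total rises by that number.

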### **4.3.2. Respiratory Infection susceptibility in athletes and elderly (II,III)**

All potential risk factors for respiratory infections will be analyzed for two different in risk populations, elderly and athletes (II,III). Elderly clinical trial will be analyzed as a completed-protocol (III).

Descriptive values for each risk factor will be calculated and Relative Risk to Respiratory Infection with the respective confidence intervals at 95% assessed.

Multiple linear regression and logistic regression models will be used as appropriate to modulate for possible confounders, namely respiratory infections and their severity will be given by questionnaire scores. Univariate and multiple logistic regression models will be developed using independent variables as risk factors for having respiratory tract infections. Results will be presented as odds ratio (OR) with [95% confidence interval (CI)].

Variables potentially included in the model for swimmers illness profile (II) will be: gender, age, BMI (variable categorized), anthropometric changes, history of respiratory tract disease, smoking habits, previous influenza immunization, probiotics consumption, vitamins consumption, sleep quality, anxiety, nutritional status, urinary metabolomic profile, asthma, bronchial hyper-responsiveness, airway inflammation presence and immunological mediators.

Variables used in the elderly intervention model will included: gender, age, BMI, history of respiratory tract disease, diabetes, smoking habits, previous influenza immunization and previous practiced exercise training.

Models will be performed by data driven and progressively adjusted considering its goodness-of-fit (assessed by Hosmer-Lemeshow test) and predictive power (evaluated by ROC curve analysis).

For the moderate exercise intervention trial in elderly (II) sample power was calculated as infrastructure conditions only allowed a maximum sample of 40 persons in each group to be included. Relative risk of having an infection in the training group and in control group will be used. In the previous published literature assessing postmenopausal women [24], having an infection during an moderate-exercise intervention, 48% had at least one episode of respiratory infections compared to control group, which had at 30% in the second. Assuming an alpha of 0.05 on exercise group had 48% change of having infection and 30% of having infections in the non-exercising group the power would be 30%.

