## **4.1.2. Respiratory Infection susceptibility in athletes-illness prone profile (II)**

This is a prospective, three month follow-up, cohort study to evaluate the risk factors for respiratory infection. A group of swimmers from a Porto sports team (Futebol Clube do Porto), from a high competition level and active during the follow-up period, which is coincident with a pre-competition season and higher incidence of respiratory infections (from January to March). During this time participants will be followed for respiratory infections episodes through a daily respiratory infections questionnaire, which is filled in when they began respiratory infections symptoms and then everyday during the scheduled-time illness. Acute respiratory infection number, duration severity of each episode will be characterized. All potential risk factors for respiratory infections will be evaluated at baseline and at the end of the study, except for urine analysis which will be collected every week and during the respiratory infection episode to establish an eventual association between changes of urinary metabolome in and outside the infection period.

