- anthropometric and bio-impedance measures;
- nutritional state assessment and nutritional questionnaires;
- sleep quality assessment questionnaires and anxiety symptoms questionnaire (Zung Self Rate Anxiety Scale-- **Attachment 4**);

All variables will be assembled at the end of the study and individuals with respiratory infections during this period will be compared with those without the outcome. Associations will be performed *a posteriori* between urine metabolome analysis and the days with respiratory infections and before/after an infection episode.

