### **Sleep and sleep quality questionnaire**

To understand and evaluate sleep quality a questionnaire will be applied, asking sleep habits and sleep quality, both addressed by the Pittsburgh Sleep Quality Index. This is a self-rated validated questionnaire that assesses sleep quality and sleep disturbances over a 1- month time interval. A score >5 is used to define a 'poor sleeper'. (**Attachment 3**)

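### Study II lists anthropometric change as a risk factor for infection, although that change spans the infection window, and it does not limit sleep, anxiety and nutritional status to baseline values

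*Protocol*

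**What the plan says.** Section 4.3.2 states the role of the variables: "Univariate and multiple logistic regression models will be developed using independent variables as risk factors for having respiratory tract infections". The candidate list for the swimmers includes "gender, age, BMI (variable categorized), anthropometric changes, history of respiratory tract disease" and, further on, "sleep quality, anxiety, nutritional status, urinary metabolomic profile". None of these carries a time point, but a change needs two measurements.

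Section 4.1.2 sets the timing. Its opening paragraph says "All potential risk factors for respiratory infections will be evaluated at baseline and at the end of the study", with weekly urine as the exception. Under Procedures, the baseline list includes body measurements, nutritional assessment, and the sleep and anxiety questionnaires. The list for the end of follow-up repeats "anthropometric and bio-impedance measures", nutritional assessment, and "sleep quality assessment questionnaires and anxiety symptoms questionnaire (Zung Self Rate Anxiety Scale". The closing paragraph then says "All variables will be assembled at the end of the study and individuals with respiratory infections during this period will be compared with those without".

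Section 4.2.2 describes the sleep index as one that "assesses sleep quality and sleep disturbances over a 1- month time interval" and the anxiety scale as measuring a state more than a personality trait.

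**The concern.** The aim of Study II is a profile of which swimmers are prone to respiratory infection. A predictor can serve that aim only if it is fixed before the infection.

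Consider a swimmer who falls ill in week 5, misses training and then gains or loses weight or skinfold thickness. At the end visit this swimmer shows an anthropometric change, and the model would count it as a risk factor for the illness that came first. The protocol keeps a diary of missed training sessions, so it expects training to be lost during follow-up.

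If such a variable enters the model, its odds ratio mixes cause with consequence and the ROC area can be inflated. The value is also not available when a coach or physician would want to apply the profile, before a season. Section 4.3.2 builds the models from the data, so a variable altered by the outcome may well be retained.

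End-of-study sleep, anxiety and nutrition raise the same question if their end values are used.

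**Working it through.** **Step 1. Timing of each variable against the outcome (sections 4.1.2 and 4.3.2).**

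| Variable in the model | When measured | Can it be formed from pre-infection data? |
|---|---|---|
| Anthropometric changes | Baseline and end visit | No: the end value follows every infection in follow-up |
| Sleep quality | Baseline and end visit | Yes, if baseline is used; visit not stated |
| Anxiety | Baseline and end visit | Yes, if baseline is used; visit not stated |
| Nutritional status | Baseline and end visit (dietary recalls also in between) | Yes, if baseline is used; visit not stated |

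The outcome is an infection during the three months between the two visits. The first row is a problem of timing and needs no arithmetic. The other three rows are problems only if end values are used, and nothing in the text rules that out.

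**Step 2. An illustration of size.** The protocol has no figure of its own on this point to reproduce.

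Inputs from the protocol:
- 40 swimmers, of whom 40% have an infection (Study II sample size paragraph): 0.40 × 40 = 16 infected, 24 not.
- Significance threshold 0.05 (section 4.3).

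Assumptions that are not in the documents:
- The variable has no effect on infection.
- Infection shifts the end value of every infected swimmer by d standard deviations.
- Values are normal with equal variance, and the groups are compared by a two-sided t-test.

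Formulas:
- Noncentrality = d × √(16 × 24 / 40) = d × √9.6 = 3.098 d. There are 38 degrees of freedom and the critical value is 2.024.
- Expected odds ratio per SD = exp(d).

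| d (assumed) | Noncentrality | Probability of p ≤ 0.05 | exp(d) |
|---|---|---|---|
| 0 (as for a baseline value) | 0 | 5.0% | 1.00 |
| 0.25 | 0.77 | 11.7% | 1.28 |
| 0.5 | 1.55 | 32.7% | 1.65 |
| 0.8 | 2.48 | 67.6% | 2.23 |

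**Step 3. Change score in place of end level.** With equal variances at the two visits and correlation r between them (r is assumed), the SD of the change is √(2(1 − r)).
- r = 0.5: the SD is 1, and the results are those of the table.
- r = 0.8: the SD is √0.4 = 0.632, so d = 0.5 becomes 0.5 / 0.632 = 0.79 SD of the change. In 20,000 simulated studies with infections drawn at 40%, the change score was significant in 65.5%, against 32.2% for the end level. Baseline values stayed between 4.9% and 5.3% in every scenario.

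**Step 4. Only some infections leave a trace.** The sleep index looks back one month of three. If infections are spread evenly and only those in the last month shift the end score, about one third of infected swimmers are affected. The mean shift is then d / 3, that is 0.17 SD for d = 0.5 and 0.27 SD for d = 0.8. The probability of p ≤ 0.05 falls to about 8% and 13%.

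**The case against.** The strongest objection concerns sleep and anxiety. A reader might infer that Study II uses the end-of-study sleep and anxiety scores as risk factors. The protocol does not say so. Section 4.3.2 names no visit, and the baseline list in section 4.1.2 presents both questionnaires among the potential risk factors screened at baseline. The sentence that compares infected with uninfected swimmers describes a group comparison, not the terms of the regression. Which visit's value enters a model is also often left to an analysis plan. This objection stands as far as it goes: end-of-study use is left open, not prescribed. It is left open, however, by the protocol's own statements that risk factors are evaluated at both visits and that all assembled variables are compared by infection status.

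For anthropometric changes the objection is weaker. The term is not defined, and it is one of 17 variables described as only potentially included. Yet end minus baseline is the natural reading, and no intermediate body measurement is scheduled from which an earlier change could be formed.

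The objection to the size also has force. No shift of 0.5 or 0.8 SD appears in the documents, and a shift common to all infected swimmers is a strong assumption. Step 4 shows how far the figures fall when only late infections matter. Nor does one optional term make the whole profile useless, since most of the other candidates are not repeated at the end visit.

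**Conclusion.** The point holds in this form. The infection model for the swimmers names a variable, anthropometric changes, that on its natural reading cannot be formed without a measurement taken after any infection in the window. It can therefore report a consequence of infection as a risk factor. For sleep quality, anxiety and nutritional status the narrower statement is right: the protocol does not limit them to baseline and compares all assembled variables by infection status.

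The timing conclusion follows from the text and rests on no assumed effect size. The figures of about 12%, 33% and 68%, against 5% for baseline values, are illustrations that depend on assumed uniform shifts of 0.25, 0.5 and 0.8 SD in an end-of-study level. They would be higher for a change score with strongly correlated visits, and lower if only some infections affect the end measure. They should not be read as an estimate of the bias in this study.

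**What to change.** In section 4.3.2:

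1. Delete anthropometric changes from the list of risk factors in the swimmers' infection model.
2. Add one sentence stating that anthropometry, nutritional status, sleep quality and anxiety enter that model at their baseline values.
3. State that end-of-study values and changes from baseline are reported separately by infection status, as possible consequences of the season or of infection. Align the comparison sentence at the end of section 4.1.2, Procedures, with this.

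The cost is a few lines of wording. Section 4.1.2 already schedules all four baseline assessments, so no visit, measurement or participant is added. The end-of-study data are still reported, in a role that their timing supports.
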